**Figure 8: Reporting of Serious Adverse Events**

The Investigator reports all SAEs within 24 h to the Sponsor. The Sponsor will report all serious and unexpected adverse drug reactions (SUSARs) in an expedited fashion to all concerned investigators, Independent Ethics Committees (IECs) and the Competent Authority.

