#### 6.3.1.3.2 Reporting of Serious Adverse Events

All SAEs that occur during the period of observation starting with signing of the informed consent and ending with the 6-Month Assessment, and all SAEs occurring up to 30 days after receiving the stem cell injection (study drug) in case of withdrawal, whether considered to be associated with the study drug or not, must be reported by the Investigator. A SAE report must be faxed within 24 hours following knowledge of the event by the Investigator to:

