**SAE [contact]-hour service)**

**Medical [contact]**

The Investigator should not wait to receive additional information to fully document the event before notifying of a SAE, though additional information may be requested. The minimum information required for an initial report is:

- Sender of report (name, address and phone number of Investigator)
- Date of initial report
- Patient identification (patient number)
- Protocol number
- Investigational medicinal product
- Description of event with outcome, if available, and criteria for seriousness, expectedness and causality

Where applicable, information from relevant laboratory results, hospital case records and autopsy reports should be obtained. The Investigator is also required to submit follow-up reports to Adverse Event Reporting until the SAE has resolved or, in the case of permanent impairment, until the SAE stabilizes. The original SAE form must then be sent by mail to the Clinical Monitor. In addition, the event must be documented in the CRF.

As required, the Sponsor, will report the SAE to the relevant Regulatory Authority and the IECs within the required timeframe, depending on the local regulations. Regulatory agencies will be notified as soon as possible but no later than 7 days after first knowledge of fatal or life-threatening unexpected AR and no later than 15 days after knowledge of the other unexpected SAR.

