#### *6.3.1.5 Adverse Events of Specific Interest*

Events that are listed in Appendix 2 are considered to be of specific interest for the purpose of this study and are monitored in detail. Documentation and reporting of Adverse Events of Specific Interest will be according to the standard procedure of SAE reporting in Section 6.3.1.3.2. continuously up to study end and furthermore as safety follow up to Assessment VI after 24 months. After study termination (Assessment V, 6-Month Follow-Up) AEs not listed as AEs of specific interest will not be documented unless they are possibly, probably or definitely related to the investigational medicinal product or result in death. In case of seriousness all possibly, probably or definitely related AEs will be reported at Assessment VI, 24-Month Follow-Up.

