- Documentation of any AE/SAE and reporting of any SAE that is related to the investigational product (relatedness 3 to 5) since last assessment; documentation of any MACE and any Event of Specific Interest since last assessment (reporting only in case of relatedness 3 to 5); see Section 6.3.1, 6.3.1.5, and 6.3.1.6

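### The protocol's rules for reporting events after month 6 disagree on scope and clock, and a known related serious event outside Appendix 2 may be held until the 24-month visit

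*Protocol*

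**What the plan says.** Five places in the protocol bear on reporting after Assessment V (month 6).

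- **Section 3.1 (Overview).** Documentation and reporting in the safety follow-up cover every event at least possibly related and every event of specific interest, with MACE and death included. No clock is given.
- **Text under Figure 8 (within 6.3.1.3.1).** "The Investigator reports all SAEs within 24 h to the Sponsor". No end date is attached.
- **Section 6.3.1.3.2.** The operative rule runs from the Investigator's knowledge: "A SAE report must be faxed within 24 hours following knowledge of the event by the Investigator to" the listed contact. Its window is limited to the period "starting with signing of the informed consent and ending with the 6-Month Assessment", or to 30 days after injection in withdrawn patients. The same section sets the regulatory deadlines: "no later than 7 days after first knowledge of fatal or life-threatening unexpected AR", and 15 days for other unexpected serious reactions.
- **Section 6.3.1.5.** Events of specific interest (Appendix 2) follow the SAE procedure of 6.3.1.3.2 "continuously up to study end and furthermore as safety follow up to Assessment VI after 24 months". The paragraph then closes with: "In case of seriousness all possibly, probably or definitely related AEs will be reported at Assessment VI, 24-Month Follow-Up".
- **Section 7.2.6.3 (24-month visit list).** It calls for "reporting of any SAE that is related to the investigational product (relatedness 3 to 5) since last assessment". For MACE and events of specific interest it adds the restriction "reporting only in case of relatedness 3 to 5".

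Table 2 shows no assessment between month 6 and month 24.

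**The concern.** A site that learns, say at month 8, of a serious event it judges related has no single instruction. The explicit 24-hour window has closed, one sentence points to the 24-month visit, and another sets 24 hours without an end date. If the event is in Appendix 2, a third sentence sends it through the standard SAE procedure. If it is an unrelated event of specific interest, section 3.1 and section 6.3.1.5 would have it reported, while the visit list would have it only documented.

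Early warning of late harm is at stake. Section 1.3 names tumour formation and unwanted tissue formation as potential risks, and tumours are among the safety parameters at Assessment VI. Appendix 2 does not list tumours, so they do not get the continuous route. Section 9.9 has the Safety Monitoring Board review class III to V events and ties termination of the trial to their frequency in the cell group. Related events held until month 24 are missing from that review in the meantime.

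**Working it through.** **Step 1. Set the rules side by side for an event after month 6.**

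| Type of event | Figure 8 text | 6.3.1.3.2 | 6.3.1.5 | 7.2.6.3 | 3.1 |
|---|---|---|---|---|---|
| Related, serious, not in Appendix 2 (e.g. tumour) | 24 h | window closed | at Assessment VI | at Assessment VI | included, no clock |
| Related, serious, in Appendix 2 | 24 h | window closed, but invoked by 6.3.1.5 | SAE procedure continuously, and also at Assessment VI | at Assessment VI | included, no clock |
| Unrelated, in Appendix 2 | 24 h if serious | window closed, but invoked by 6.3.1.5 | SAE procedure continuously | documented, not reported | included, no clock |

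- Row 1: 6.3.1.5 and 6.3.1.3.2 do not conflict, because the window has ended. There is a gap. The conflict is with the Figure 8 text.
- Row 2: 6.3.1.5 gives two reporting points for the same event.
- Row 3: 6.3.1.5 and 3.1 include events that the restriction in 7.2.6.3 leaves out.

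**Step 2. Longest delay.** Inputs: Assessment V at month 6, Assessment VI at month 24, each ± 2 weeks (Table 2).

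- 24 − 6 = 18 months, which reproduces the 18-month safety follow-up stated in section 3.1.
- With both visit windows the interval is 17.1 to 18.9 months.
- This is the maximum, for an event just after month 6. An event at month 23 waits about 1 month.

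**Step 3. Overlap with treatment of other patients.** Inputs: 142 patients (section 8.7) and 5 years = 60 months of recruitment (section 3.1). Uniform accrual is an assumption that the protocol does not state.

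- Rate: 142 / 60 = 2.37 patients per month.
- A patient's months 6 to 24 lie wholly within recruitment if the operation falls in the first 60 − 24 = 36 months (36/60 = 60% of patients), and at least partly within it if in the first 60 − 6 = 54 months (54/60 = 90%).
- A month-8 event held to month 24 waits 16 months. For a patient operated on at recruitment month m, the number randomized meanwhile is min(16, 60 − (m + 8)) × 2.37:
  - m up to 36: 16 × 2.37 = 37.9, about 38; with 1:1 allocation about 19 to cells.
  - m = 50: 2 × 2.37 = 4.7, about 5.
  - m = 52 or later: 0.

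**The case against.** Several stronger readings are tempting, and the text does not carry them.

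- **A reader might infer that 6.3.1.5 breaks the 24-hour rule of 6.3.1.3.2 and the 7- and 15-day limits.** The 24-hour window in 6.3.1.3.2 has expired by month 6, so for events outside Appendix 2 nothing there is contradicted. The 7- and 15-day limits run from knowledge. If the sponsor's knowledge is meant, a late site report delays them without clearly breaching them.
- **A reader might infer that late arrhythmias would go unreported.** Ventricular and supraventricular arrhythmia are Appendix 2 events, and 6.3.1.5 gives them a continuous SAE route. For them the defect is only that the closing sentence and the visit list blur that route.
- **A reader might infer that sites are ordered to withhold known events, or that the Safety Monitoring Board could not act.** Nothing forbids earlier reporting. The closing sentence of 6.3.1.5 can also be read as defining which events are taken up at the only scheduled contact, and other visit lists use the same since-last-assessment phrasing for documentation. The Board still receives class III to V events and has the Appendix 2 route.

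Two further points are fair. The 18 months count from occurrence and the 24 hours from knowledge. With no contact scheduled between months 6 and 24, part of any delay is late knowledge, which reporting wording alone does not remove. Also, section 6.3.1.3.1 opens by referring to the course of the study, and section 3.1 places Assessment VI outside the study, so the Figure 8 sentence might be read as bounded, although it states no end date.

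What does not yield is the combination. 6.3.1.5 names a visit as the reporting point, 7.2.6.3 uses the word reporting and covers the whole interval, and the operative window has closed. A safety clause should not rest on a charitable reading. The conflicts in rows 2 and 3 of the table remain whichever way the Figure 8 sentence is taken.

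**Conclusion.** The concern holds as an inconsistency with a safety consequence. Section 3.1, the Figure 8 text and sections 6.3.1.3.2, 6.3.1.5 and 7.2.6.3 do not agree on which events after month 6 are reported, or by what clock. Section 6.3.1.5 is inconsistent with itself for serious related Appendix 2 events. For a related serious event outside Appendix 2, the text permits a site to hold a known event until the 24-month visit.

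The delay is at most about 18 months from occurrence, and shorter for events later in the interval. It postpones the expedited reporting in 6.3.1.3.2 and the review in 9.9. The figure of about 38 patients randomized meanwhile (about 19 to cells) is an upper value for a month-8 event. It requires uniform accrual, an index patient operated on by month 36, and a site that knows of the event at once and holds it. It falls to about 5 for a patient operated on at month 50. The protocol gives no expected number of such events, so the total effect cannot be sized.

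**What to change.** - In 6.3.1.5 and 7.2.6.3, state that related serious events after month 6 are reported within 24 hours of the Investigator's knowledge, up to and including Assessment VI, in place of reporting at that visit.
- In 6.3.1.3.2, extend the reporting window to match.
- Reconcile section 3.1, the Figure 8 text, 6.3.1.5 and 7.2.6.3 on whether unrelated events of specific interest, MACE and deaths after month 6 are reported or only documented. The sponsor has to make this choice; the documents support either answer in different places.

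The cost is protocol wording in a few sections and a few more expedited reports. No visit, endpoint or analysis changes.

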#### *6.3.1.6 Major Adverse Cardiovascular Events – MACE*

Major adverse cardiovascular events patient alive no/yes, reoperation no/yes, secondary ICU admission no/yes, infarction post-OP no/yes, readmission no/yes, reintervention no/yes, new ventricular arrhythmia no/yes) will be separately assessed at Assessment V (6 months after OP) and 24-Month Follow-Up.

### **6.3.2 The Methods and Timing for Assessing and Recording Other Safety Parameters**

The methods for assessing safety parameters consist of clinical routine methods for observation of patients after CABG surgery (i.e. ECG, laboratory tests including human immunodeficiency virus [HIV], hepatitis B virus [HBV] and hepatitis C virus [HCV] status, Treponema pallidum), plus those that are required by the study protocol (i.e. echocardiography, Holter, ECG). They will be recorded on special AE case report forms.

An obligatory safety follow up is planned for further 18 months after study data closure. Therefore the patients will be required to attend Assessment VI 24 months after the operation. This will be outside the study after data closure. At Assessment VI patient will

undergo examination of all safety parameters and will be asked to complete QoL questionnaires.

### 6.3.2.1 Laboratory Parameters

Laboratory assessments will be performed locally at each center's laboratory by means of their established methods. Before starting the study, the Investigator will supply the Sponsor with a list of the normal ranges and units of measurement. The following laboratory parameters will be determined in accordance with the Schedule of Assessments (Table 2).

**Table 1: Laboratory Assessments**

|                                                           |                                                              |                               |
|-----------------------------------------------------------|--------------------------------------------------------------|-------------------------------|
| Hematology: (2,7 mL EDTA)                                 | Hemoglobin (mmol/L or g/dL)                                  |                               |
|                                                           | Leukocytes ( $10^9$ /L or /nL or tsd/ $\mu$ L)               |                               |
|                                                           | Thrombocytes ( $10^9$ /L or /nL or tsd/ $\mu$ L)             |                               |
| Clinical chemistry (5 mL Li-Heparin, electrolytes incl.): | C-reactive protein (CRP) (mg/L or mg/dL)                     |                               |
|                                                           | Creatinine ( $\mu$ mol/L or mg/dL)                           |                               |
|                                                           | Creatine Kinase (CK) (U/L)                                   |                               |
|                                                           | Creatine Kinase MB (CK-MB) (U/L)                             |                               |
|                                                           | Troponin T (TNT) (ng/mL or $\mu$ g/L)                        |                               |
| Blood lipids                                              | Total cholesterol (mmol/L or mg/dL)                          |                               |
|                                                           | LDL cholesterol (mmol/L or mg/dL)                            |                               |
|                                                           | HDL cholesterol (mmol/L or mg/dL)                            |                               |
|                                                           | Triglycerides (mmol/L or mg/dL)                              |                               |
| Electrolytes:                                             | Sodium (Na+) (mmol/L)                                        |                               |
|                                                           | Potassium (K+) (mmol/L)                                      |                               |
| NT-proBNP (2.7 mL, EDTA)                                  | NT-proBNP (pg/mL)                                            |                               |
| Serology (10 mL serum):                                   | Anti HIV 1/2                                                 | positive/negative             |
|                                                           | HBsAG                                                        | positive/negative             |
|                                                           | Anti-HBc-IgG                                                 | positive/negative             |
|                                                           | Anti HCV                                                     | positive/negative             |
|                                                           | Treponema pallidum                                           | positive/negative             |
|                                                           | if Anti-HBc-IgG positive:                                    |                               |
|                                                           | HBV-NAT                                                      | positive/negative             |
|                                                           | Anti-HBs AK                                                  | quantified ( $\geq 100$ IU/L) |
| HAMA: (2.7 mL serum)                                      | HAMA Titer ( $\geq$ or $< 1:1000$ , if applicable)           |                               |
| Pregnancy test:                                           | Serum pregnancy test in women of childbearing potential only |                               |

Titer of HAMA will only be determined in case of known hypersensitivity. Laboratory abnormalities (normal ranges see **Fehler! Verweisquelle konnte nicht gefunden werden.**) should be recorded as AEs after Investigator judgment.

#### 6.3.2.2 *Vital Signs*

The following vital signs examination will be assessed in accordance with the Schedule of Assessments (Table 2)

- Supine blood pressure in mm/Hg
- Classification of blood pressure according to the ESC/ESH guidelines 2007
- Resting pulse rate in beats/min
- Body temperature in °C (aural)
- Body weight in kg
- Respiratory rate in breaths/min

#### 6.3.2.3 *General Physical Examination*

- Examination of head, neck, thorax, abdomen, neurological system, musculoskeletal system, skin, others (except heart) and record any pathological findings (no/yes, if yes: describe)

#### 6.3.2.4 *Holter and LOWN Classification*

The electrical activity of the heart will be recorded at the Assessments Screening, Hospital Discharge, 6-Month Follow-Up and 24-Month Follow-Up (Table 2). VES in %, SVES in %, incidence of VT, maximum frequency in beats/min, and number will be documented. The occurrence of tachycardial arrhythmia will be assessed according to the LOWN classification. Historic data (not older than 4 weeks) may be used except for Assessment Hospital Discharge.

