### 4.1 Inclusion Criteria

Patients will be entered into this study only if they meet all of the following criteria:

1. Coronary artery disease after myocardial infarction with indication for CABG surgery
2. Currently reduced global LVEF assessed at site by cardiac MRI at rest ( $25\% \leq \text{LVEF} \leq 50\%$ )
3. Presence of a localized akinetic/hypokinetic/hypoperfused area of LV myocardium for defining the target area
4. Informed consent of the patient
5.  $18 \text{ years} \leq \text{Age} < 80 \text{ years}$
6. Are not pregnant and do not plan to become pregnant during the study. Females with childbearing potential must provide a negative pregnancy test within 1-7 days before OP and must be using oral or injectable contraception (non-childbearing potential is defined as post-menopausal for at least 1 year or surgical sterilization or hysterectomy at least 3 months before study start).

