### 4.2 Exclusion Criteria

Patients will be entered into this study only if they meet none of the following criteria:

1. Emergency operation
2. Presence of any moderate-severe valvular heart disease requiring concomitant valve replacement or reconstruction
3. Medical History of recent resuscitation in combination with ventricular arrhythmia classified by LOWN  $\geq$  class II
4. Acute myocardial infarction within last 2 weeks
5. Debilitating other disease: Degenerative neurologic disorders, psychiatric disease, terminal renal failure requiring dialysis, previous organ transplantation, active malignant neoplasia, or any other serious medical condition that, in the opinion of the Investigator is likely to alter the patient's course of recovery or the evaluation of the study medication's safety
6. Impaired ability to comprehend the study information
7. Absence of written informed consent
8. Treatment with any investigational drug within the previous 30 days
9. Apparent infection (c-reactive protein [CRP]  $\geq 20 \text{ mg/L}$ , fever  $\geq 38.5^\circ \text{C}$ )
10. Contraindication for MRI scan
11. Immune compromise including Anti HIV 1/2, HBsAg, Anti-HBc-IgG, Anti HCV, Treponema pallidum
12. Pregnant or breast feeding
13. Childbearing potential with unreliable birth control methods
14. Have previously been enrolled in this study, respectively phase I and phase II

15. Known hypersensitivity or sensitization against murine products and human-anti-mouse-antibody-titer  $\geq 1:1000$
16. Contraindication to bone marrow aspiration
17. Known hypersensitivity against iron dextrane

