## 7.2 Observations by Visit

### 7.2.1 *Screening (Assessment I; Day -7 to Day -1)*

- Inform patient about clinical trial (record in appropriate documentation)
- Obtain written informed consent, record date and time of informed consent (see Section 9.7)
- Demographic details: height in cm, year of birth, gender
- General medical history (see Section 6.3.2.6)
- Cardiac medical history (see Section 6.3.2.7)
- Risk factors (see Section 6.3.2.8)
- In- and exclusion criteria (see Sections 4.1 & 4.2)
- Vital signs (see Section 6.3.2.2)
- General physical examination (see Section 6.3.2.3)
- Blood sampling for serology (see Section 6.3.2.1)
- Blood sampling for laboratory tests (see Section 6.3.2.1)
- Blood sampling for NT-proBNP (pg/mL; to be sent to Core Lab) and HAMA in case of known hypersensitivity (see Section 6.3.2.1)
- Serum pregnancy test (female patients of childbearing potential only, see Section 6.3.2.1)
- Cardiac MRI scan and echocardiography to be sent to Core Lab (see Sections 6.1.1 & 6.1.2, 6.1.5 & 6.1.6), value for LVEF within 12 hours from MRI Core Lab
- Classification of heart failure with NYHA and angina with CCS (see Section 6.1.3)
- Heart catheterization (see Section 6.1.4)
- Holter and LOWN classification (historic data may be used, see Section 6.3.2.4)
- 12-lead ECG (see Section 6.3.2.5)
- Completion of QoL questionnaires (MLHF and SF-36; see Section 6.2)
- 6-Minute Walk Test (6MWT, see Section 6.1.7)
- Documentation of AEs/SAEs during screening procedure (see Section 6.3.1)
- Concomitant medication, platelet aggregation inhibitors during the last 2 weeks (see Section 5.7)
- Determine patient's eligibility for enrollment (PI and study physician or at least two study physicians). Give reason in case patient is not eligible.

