#### 7.2.6.2 *6-Month Follow-Up post OP ( $\pm 2$ weeks, Assessment V)/Early Termination*

- Study termination
  - has the study been terminated according to protocol? If yes, proceed with Physical examination/vital signs
  - If study was early terminated:
    - Date of withdrawal/early termination
    - Reason for withdrawal/early termination (AE, at the discretion of the investigator, violation of eligibility criteria, deviation from the treatment plan specified in the protocol, pregnancy, patient withdraws consent, death, other (describe))
- Date of patient contact
- Vital signs (see Section 6.3.2.2)
- General physical examination (see Section 6.3.2.3)
- Blood sampling for laboratory tests (Hematology, Clinical Chemistry and Electrolytes; see Section 6.3.2.1)
- Blood sampling for NT-proBNP (pg/mL; to be sent to Core Lab; see Section 6.3.2.1)
- Cardiac MRI scan and echocardiography to be sent to Core Lab (see Sections 6.1.1 & 6.1.2, 6.1.5 & 6.1.6)
- Classification of heart failure with NYHA and angina with CCS (see Section 6.1.3)
- Holter and LOWN classification (historic data may be used, see Section 6.3.2.4)
- 12-lead ECG (see Section 6.3.2.5)
- Determination of MACE (see Section 6.3.1.6)
- Completion of QoL questionnaires (MLHF and SF-36; see Section 6.2.)
- 6-Minute Walk Test (6MWT, see Section 6.1.7)
- Documentation of any change in concomitant medication
- Documentation of any AE/SAE since last assessment

*7.2.6.3 24-Month Follow-Up post OP ( $\pm$  2 weeks, Assessment VI after data closure for safety reason)*

- Date of patient contact
- Vital signs (see Section 6.3.2.2)
- General physical examination (see Section 6.3.2.3)
- Echocardiography from practice based cardiologist (see Sections 6.1.1, 6.1.2, & 6.1.6)
- Holter from practicing cardiologist and LOWN classification (see Section 6.3.2.4)
- Blood sampling for laboratory tests (Hematology, Clinical Chemistry and Electrolytes; see Section 6.3.2.1)
- Blood sampling for NT-proBNP (pg/mL; to be sent to Core Lab; see Section 6.3.2.1)
- Completion of QoL questionnaires (MLHF and SF-36; see Section 6.2.)
- Performance of 12-lead ECG (see Section 6.3.2.5)
- Determination of MACE (see Section 6.3.1.6)
- Documentation of concomitant medication related to treatment of AE/SAE

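### A screening Holter may be up to 4 weeks old while infarcts just over 2 weeks old are eligible, so the only pre-treatment arrhythmia baseline can predate the infarct

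*Protocol*

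**What the plan says.** Section 6.3.2.4 sets the Holter schedule: "The electrical activity of the heart will be recorded at the Assessments Screening, Hospital Discharge, 6-Month Follow-Up and 24-Month Follow-Up (Table 2"). It then allows earlier recordings: "Historic data (not older than 4 weeks) may be used except for Assessment Hospital Discharge". The visit lists in 7.2.1 (screening) and 7.2.6.2 (6 months) repeat the permission: "Holter and LOWN classification (historic data may be used, see Section 6.3.2.4").

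The population is post-infarct by definition. Inclusion criterion 1 reads "Coronary artery disease after myocardial infarction with indication for CABG surgery". The only limit on how recent the infarct may be is exclusion criterion 4: "Acute myocardial infarction within last 2 weeks". Section 7.2.1 places screening at "Screening (Assessment I; Day -7 to Day -1").

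Ventricular arrhythmia is among the potential risks of the cell therapy in section 1.3. Section 6.3.1.6 records it at 6 and 24 months as "new ventricular arrhythmia no/yes". Table 2 gives Assessments V and VI a window of plus or minus 2 weeks.

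No section requires an earlier screening Holter to have been made after the infarct. The general rule in 6.1 on examinations made before consent asks only that they were done according to the protocol. The withdrawal rule in 4.3 deals with infarcts between recruitment and surgery, not with those before recruitment.

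**The concern.** The look-back for the Holter (4 weeks) is longer than the look-back for the infarct (2 weeks). A patient can be eligible with an infarct that falls between the Holter and screening. The recording then describes the rhythm of a heart that had not yet had that infarct.

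This matters because Table 2 schedules one Holter before treatment. The next, at discharge, follows the injections. Calling an arrhythmia new after surgery needs a valid earlier reference. If that reference predates the infarct, ectopy caused by the infarct can look as though it arose after treatment. The protocol already accepts the principle at one point: it bars earlier recordings at discharge, where an old record could predate the operation. The same reasoning applies to an infarct inside the screening look-back, which the text does not cover.

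A second, looser point concerns follow-up. The 4-week allowance also applies at 6 and 24 months, where it is longer than the visit tolerance of 2 weeks on either side.

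**Working it through.** The protocol gives no figure on this point to reproduce. The check is day arithmetic on its own limits.

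**Inputs.** Holter at most 28 days old (6.3.2.4). Infarct more than 14 days old, so 15 days at the least (exclusion criterion 4). Screening on Day -7 to Day -1 (7.2.1). The protocol does not say whether either limit is counted from screening or from the operation (Day 0), so all combinations are shown.

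**Step 1: can the baseline predate the infarct?** Lead = day of youngest eligible infarct minus day of oldest permitted Holter.

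| Screening day | Holter limit from | Infarct limit from | Holter day | Infarct day | Lead (days) |
|---|---|---|---|---|---|
| -7 | screening | screening | -35 | -22 | 13 |
| -7 | screening | operation | -35 | -15 | 20 |
| -7 | operation | screening | -28 | -22 | 6 |
| -7 | operation | operation | -28 | -15 | 13 |
| -1 | screening | screening | -29 | -16 | 13 |
| -1 | screening | operation | -29 | -15 | 14 |
| -1 | operation | screening | -28 | -16 | 12 |
| -1 | operation | operation | -28 | -15 | 13 |

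The lead is 6 to 20 days and positive under every reading. With one common reference date, the infarct ages at risk are 15 to 27 days, because a 28-day-old Holter must be older than the infarct.

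**Step 2: how many patients?** The documents give no distribution of infarct age and no share of earlier Holters, so these are assumptions: 5 to 15% of patients have an infarct about 15 to 28 days old, and half of them use an earlier Holter.

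- Patients in the overlap group: 142 × 0.05 × 0.5 = 3.6 to 142 × 0.15 × 0.5 = 10.7.
- A baseline in this group is pre-infarct only if the Holter is older than the infarct. With Holter age uniform on 0 to 28 days and infarct age *a* uniform on 15 to 28 days, the chance is (28 − *a*)/28. The mean of *a* is 21.5, so the average chance is 6.5/28 = 0.23.
- Affected baselines: 3.6 × 0.23 = 0.8 to 10.7 × 0.23 = 2.5, or about 1 to 3 of 142.

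**Step 3: follow-up visits.** Taking 6 months as 26 weeks, the visit window opens at week 24.

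- Visit on target: the oldest permitted Holter is from week 22, 14 days before the window opens.
- Earliest permitted visit: 26 − 2 − 4 = week 20, 28 days before it opens.
- Latest permitted visit: 26 + 2 − 4 = week 24, exactly on the edge.

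The same differences apply at month 24.

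**The case against.** The case against giving this weight is strong, and most of it stands.

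**Size.** A reader might count every patient with a recent infarct and an earlier Holter, about 4 to 11 of 142 under the assumed shares. That is too many, because the Holter must also be older than the infarct. Even 1 to 3 may be generous, since it treats a Holter as equally likely before an unforeseen infarct and after it.

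**Exclusion criterion 3.** A reader might infer that a patient could pass this criterion on a recording made before the resuscitation it concerns. The protocol does not support that. The criterion is one of history ("Medical History of recent resuscitation in combination with ventricular arrhythmia classified by LOWN" class II or above), and no section says it is judged from the Holter alone. General history must be no older than 24 hours (6.3.2.6), cardiac history grades ventricular arrhythmia (6.3.2.7), a 12-lead ECG is done at screening (6.3.2.5), and at least two physicians decide eligibility (7.2.1). The ECG cannot replace the Holter as a baseline, since it gives no hourly ectopy count for LOWN classes I and II. Together, however, these safeguards make a missed resuscitation unlikely.

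**MACE.** A reader might infer that the MACE endpoint as a whole rests on the screening Holter. The definitions in 3.2 and 8.8 list ventricular arrhythmia without requiring it to be new. Only 6.3.1.6 uses that word, and it does not define it against the screening Holter. Section 8.6 names no Holter change-from-baseline analysis.

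**Bias.** The allowance applies to both arms of a blinded trial randomized within site, so it produces noise rather than an evident difference between arms.

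**Follow-up visits.** A reader might call the 4-week allowance at month 6 a contradiction of Table 2. It is an explicit exception for the Holter, repeated in the month-6 visit list, and can be read as deliberate. Section 6.1 also gives a reason for reusing earlier examinations: sparing the patient inconvenience and risk.

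What remains is the gap at screening. None of these arguments supplies a requirement that the baseline Holter follow the infarct.

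**Conclusion.** The gap is real under every reading of the reference dates, but minor. For an infarct about 15 to 27 days old, the sole pre-treatment Holter/LOWN baseline may predate the infarct by up to 13 days when both limits are counted from the same date (6 to 20 days at the extreme across the readings). The likely number is about 1 to 3 of 142 patients. That rests on assumed shares of 5 to 15% and one half, and on uniform ages, none of which the protocol provides.

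The consequence is confined to the Holter/LOWN safety data and the new-arrhythmia item of 6.3.1.6, where it adds non-differential misclassification. LVEF by MRI, the sample size and the significance level are unaffected, and no failure of exclusion criterion 3 is shown. At Assessments V and VI the 4-week allowance is a looseness to reconcile with Table 2, not an error.

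**What to change.** In 6.3.2.4, accept an earlier Holter at screening only if it was recorded after the most recent infarct; otherwise perform the Holter that Table 2 already schedules. This works whichever date the two limits are counted from. It can be checked without new data, because 6.3.2.8 already collects the date of the last infarct.

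In the same section, reconcile the 4-week allowance at Assessments V and VI with the window of plus or minus 2 weeks in Table 2, and say whether it is a deliberate exception.

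The cost is a wording change and a few Holters that can no longer be taken from earlier records. No procedure is added, and earlier recordings made after the infarct stay usable.
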